## Background

Based on a recent review, each year 38.2% of the EU population suffers from a mental disorder. Depression has been identified as the most disabling disease affecting about 17% of the population during their lifetime [1]. According to the WHO, depression will be the second most frequent illness and will carry the highest load of impairment of quality of life worldwide in 2020. Parental chronic depression is also a heavy burden for children [2]. Only 50% of all depressed patients recover within six months and two-thirds within one year, while 6% to 7% are still depressed after 10 to 15 years. There is a high danger of a chronic course of depression, as 30% of all episodes of depression last longer than two years. Half of the patients relapse after their first episode, 70% after the second, and 90% after their third episode [3]. While medication has evolved as the most frequent first-line approach to the treatment of depression, 20% to 30% of patients have not responded to medication; one-third of those responding relapse within one year, and 75% relapse within five years.

In more than 80 randomized controlled trials (RCTs), cognitive behavioral therapy (CBT) has been established as an effective treatment for depression [4-6]. In a recent meta-analysis [7] based on 23 studies totaling 1,365 subjects, this could also be established for short-term psychodynamic psychotherapy (STPP). Compared with other psychotherapies (usually CBT), a small but significant effect size (*d* = −0.30) was found, indicating the superiority of other psychotherapies immediately post-treatment, but no significant differences were found at 3-month (*d* = −0.05) and 12-month (*d* = −0.29) follow-ups.

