So far, the evidence for psychotherapy of depression rests on short-term treatments [6-8]. Unlike the results for the treatment of acute depression, psychotherapy, findings of the effects for chronic depression (dysthymia or major depressive episodes) have been limited [8]. In addition, short-term treatments offered in randomized controlled trials lack external validity. Unlike the treatments performed in clinical trials, psychotherapies in clinical practice throughout Europe are of considerably longer duration (CBT up to 60 sessions, psychodynamic treatment up to 80, psychoanalysis up to 240 to 300 sessions). Positive long-term effects of psychoanalysis and psychoanalytic long-term treatments were shown in a representative, multi-perspective and retrospective study [9]. Yet, up until now, there are no controlled studies available comparing psychoanalysis (PAT) and cognitive behavior therapy (CBT) directly [10,11]. However, a few clinical reports [12] comparing psychoanalytic and cognitive-behavioral long-term therapy exist. They demonstrate that even when psychoanalysts and behavior therapists treat similar disorders with similar success rates, the patients differ in many ways.

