### Patient preferences

Patient preferences have been identified as one of the three key components of evidence-based medicine, along with the best available research and clinical expertise. They can be defined as the behaviors or attributes of the therapist or therapy that patients value or desire. Regardless of the therapeutic model, engaging patients to become active in psychotherapy is a crucial variable [13]. Patient preferences are particularly important in psychoanalytic long-term therapies with chronically, severely ill patients who have already undergone several unsuccessful therapies [9].

Role preferences involve the behaviors and activities that clients desire themselves and their therapists to engage in while in therapy (for example, preferring the therapist to take an active advice-giving or a listening role, preferring a group or an individual format). Therapist preferences entail characteristics that clients hope their therapists will possess (for example, extended clinical experience, similar ethnic background). Treatment preferences include specific desires for the type of intervention that will be used (for example, a behavioral or a psychodynamic approach, psychotherapy or pharmacotherapy).

A recent meta-analysis [14] of 35 studies found that patients who were matched to their preferred treatment were less likely to drop out (OR = 0.59; *P* < 0.001) and showed greater improvement (*d* = 0.31; *P* < 0.001). Type of preference (role, therapist, treatment) had no specific effect, but type of design was a significant moderator with greatest effects in RCTs. Assignment by chance may or may not meet a patient’s preference. Patients with strong preferences may refuse randomization and therefore threaten the external validity of an RCT.

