### Participants

We include patients between 21 and 60 years of age suffering from chronic depression. Patients have to be depressed for more than one year and currently meet a diagnosis of major depression or dysthymia. In addition, their current depression has to be of a certain severity, meeting a Beck Depression Inventory (BDI - self-report) score above 17 and aclinician-rated Quick Inventory of Depressive Symptoms (QIDS-C) score of more than 10 points. These inclusion criteria and the exclusion criteria are listed in Table 1. Patients can be on antidepressant medication but still meet the inclusion criteria. Patients on medication have to be on a stable dosage for more than four weeks. After information and discussion of the study protocol, the required assessments over three years, and the study interventions, patients have to sign an informed consent sheet before starting baseline assessment and either preferred or randomized treatment.

**Table 1 T1:** Inclusion and exclusion criteria

Inclusion criteria	▪Diagnosis of major depression or dysthymia (based on Structured Clinical Interview - SCID) for at least 12 months
	▪QIDS-C score > 10; BDI 2 >17
	▪Complaints for at least 12 month
	▪Age: 21 to 60 years
	▪Sufficient knowledge of the German language
	▪Informed consent with the study protocol
Exclusion criteria	▪Current or past psychotic symptomatology, schizoaffective, schizophrenic, or bipolar affective disorder
	▪Substance dependence current or during the last three years
	▪Dementia
	▪Borderline, schizotypal and antisocial personality disorder
	▪Acute suicidality
	▪Restriction of intellectual capacity
	▪Serious physical illness that strongly affects the depression or is causal for the depression
	▪Concurrent psychotherapeutic treatment

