### Hypotheses

A. Effectiveness and comparison of the two treatments with the chronically depressed: Both psychotherapies lead to positive effects concerning (a) the reduction of depressive symptoms (QIDS, BDI), (b) the proportion of remitted patients (LIFE), (c) improved social functioning (SOFAS), (d) a decrease of continuous antidepressant medication. These effects are manifested at the main assessments (see Table 2: t4, t6, t8) a cross the trial. The courses of change differ between PAT and CBT: (a) CBT achieves faster symptom reduction, (b) PAT starts slowly but achieves more stable, lasting effects (this is evidenced in the process measures, the rates of response and the symptom level at follow-up (see Table 2: t6, t8, t10).

B. Comparison of preferred and randomized therapies: Preferred therapies are expected to lead to stronger effects and less study drop-outs than randomized therapies. Patient preference is particularly important in PAT. Therefore, we expect larger effect differences between PAT preference and PAT randomization compared with CBT.

C. Health costs and cost effectiveness. We expect a significant reduction of the days of absence from work and of further treatment needed (for example, hospitalization) for both therapies. We expect larger health-cost reductions for PAT compared with CBT in the long term. We expect that treatment costs for CBT will be lower than those for PAT, resulting in a better cost-benefit ratio.

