### Design

The trial will include about 360 chronically depressed outpatients. About 180 patients will have a clear preference foreither PAT or CBT. After baseline assessment (t0) they will be assigned to a study therapist offering the preferred intervention. About 180 patients will come without preference and accept to be randomized to either PAT or CBT. Randomization will take place after baseline assessment (t0). Figure1 summarizes the 2 (preference) by 2 (psychotherapies) by 4 (time) factorial design.

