### Randomization

As Figure1 shows, in a partial randomization preference trial, patients are asked if they have a preference for one specific treatment (PAT or CBT). Treatments are outlined to them in terms of a general description (see box for the instructions). If they articulate a specific preference, they are assigned accordingly (preference arm). If they articulate no specific preference, they are randomized (randomization arm).

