### Statistical analysis

The design is an analysis of variance design with repeated measures: The main factor is the form of treatment (CBT or PAT) and assignment (preference or randomization). Four main assessments encompass the treatment phase and follow-up. The variability of intake symptoms is controlled as a covariate. To determine the time factor, ANCOVAs with repeated measures and linear regression with autocorrelated data (compound symmetric covariance structure models) are applied. Dichotomous response scores are examined by tests for frequency distributions and procedures of survival analysis (Coxregression, log-ranktests). It is also tested whether differences between CBT and PAT depend on assignment (preference vs. randomization), that is, if a naturalistic selection brings clearer differences than random assignment.

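### Intake symptoms are the only covariate named for a model with self-selected contrasts; antidepressant use at intake, one plausible confounder, could be added at almost no cost

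*Protocol article*

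**What the plan says.** The Statistical analysis section sets up one repeated-measures model with two between-patient factors, form of treatment (CBT or PAT) and assignment (preference or randomization). It names one covariate: "The variability of intake symptoms is controlled as a covariate". It also announces a test of whether the PAT-CBT difference depends on assignment.

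The Randomization section explains how patients reach the arms. Those who state a preference receive the preferred treatment, and only those without one are randomized. Under Hypotheses, part B gives the first self-selected contrast a directional expectation: "Preferred therapies are expected to lead to stronger effects and less study drop-outs than randomized therapies". The Discussion makes the comparison of preference with randomization one of two major goals and says that the design can determine the impact of preference on outcome.

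On medication, the Participants section says: "Patients can be on antidepressant medication but still meet the inclusion criteria". Users must have been on a stable dose for more than four weeks. Medication appears again only as an outcome (hypothesis A, part d) and as a cost item (Objectives). The article mentions no adjustment, stratification or matching on it.

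**The concern.** Adjusting for the intake score alone suits a randomized comparison, where the covariate mainly adds precision. Here the same model also serves effects that randomization does not protect, and for those the covariates are the only guard against differences in patient mix.

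Two effects are exposed. The preference-versus-randomization effect compares two self-selected groups. The treatment main effect averages over both arms, so part of it compares patients who chose PAT with patients who chose CBT.

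Antidepressant use is a reasonable candidate confounder for three reasons.
- The Background reports, of clinical comparisons of the two long-term therapies, that "even when psychoanalysts and behavior therapists treat similar disorders with similar success rates, the patients differ in many ways".
- The section on patient preferences calls preferences particularly important in long-term psychoanalytic therapy with "chronically, severely ill patients who have already undergone several unsuccessful therapies".
- The Background states that "20% to 30% of patients have not responded to medication". A patient who still exceeds the entry cut-offs on a stable dose may therefore have a different outlook from an unmedicated patient with the same score.

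If the medicated share differs between the groups, part of that difference could be read as an effect of preference or of treatment. It could inflate a real effect or hide one.

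**Working it through.** The article states no figure on this point, so there is nothing to reproduce. The check asks how large the bias could be.

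**Inputs from the article**
- Test level 0.025 two-sided (Sample size calculation; Secondary analyses), so z = 2.241.
- Sample size: 240 in total with 60 per arm (Abstract), or about 360 split 180 and 180 (Design). Both are used. An equal split of the 180 gives 90 per cell.
- d = 0.31 for matching patients to a preferred treatment, from the cited meta-analysis (Patient preferences).

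**Assumed inputs, because the article gives none**
- Outcome gap at t4 between medicated and unmedicated patients with the same intake score: 0.2, 0.3 or 0.4 SD.
- Difference in medicated share between the groups compared: 10, 20 or 30 percentage points.
- Outcome SD of 1; 40% medicated overall (used only for the cost).

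**Step 1. Bias = gap × imbalance**
- Low: 0.2 × 0.10 = 0.02 SD
- Middle: 0.3 × 0.20 = 0.06 SD
- High: 0.4 × 0.30 = 0.12 SD

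Divided by 0.31, these are 6%, 19% and 39% of the cited preference effect.

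**Step 2. False-positive rate with no true difference**

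Rate = 1 − Φ(2.241 − bias/SE) + Φ(−2.241 − bias/SE), with SE = √(2/n) for n patients per group.

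For preference versus randomization the full bias applies. For the treatment main effect, suppose the imbalance exists only among preference-arm patients, who make up half of each treatment group. The bias is then halved, to 0.01, 0.03 and 0.06 SD.

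| Effect | n per group | SE | Low | Middle | High |
|---|---|---|---|---|---|
| Preference vs randomization | 120 | 0.129 | 2.7% | 4.1% | 9.6% |
| Preference vs randomization | 180 | 0.105 | 2.8% | 5.0% | 13.5% |
| PAT vs CBT, both arms pooled | 120 | 0.129 | 2.5% | 2.9% | 4.1% |
| PAT vs CBT, both arms pooled | 180 | 0.105 | 2.6% | 3.1% | 5.0% |
| PAT vs CBT, randomization arm only | 60 or 90 | – | 2.5% | 2.5% | 2.5% |

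The last row follows from randomization: the expected imbalance is zero.

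**Step 3. Price of the covariate**

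With equal groups, R² of group on medication = 0.25 × (imbalance)² / (0.4 × 0.6), and the SE is multiplied by 1/√(1 − R²).
- Shares 35% and 45%: R² = 0.0025/0.24 = 0.0104, SE × 1.005.
- Shares 25% and 55%: R² = 0.0225/0.24 = 0.0938, SE × 1.05.

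This is before any precision gained from variance that medication explains.

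**The case against.** **The article is a condensed plan.** It does not say that intake symptoms are the only covariate, and the full protocol or analysis plan may add others. That lowers the weight. The point survives because the article states a covariate choice that suits a randomized comparison, applies it to a self-selected one, and announces a hypothesis on the result.

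**Nothing singles out antidepressant use.** This largely stands. No passage links medication to having a preference or to choosing PAT over CBT. The Background sentence on differing patients does not mention medication, and it reports similar success rates. The non-response figure is general, and past non-responders may be unmedicated at intake, so a yes/no flag captures the mechanism only in part. Chronicity, childhood trauma, personality diagnosis and site are also candidates. Antidepressant use is proposed because eligibility already requires it to be established, not because it is shown to be the strongest confounder.

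**The data may not be there.** Table 2 lists no medication instrument at t0. But the stable-dose rule cannot be applied without asking about medication, and hypothesis A(d) needs a starting value.

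**The non-randomized nature is disclosed.** The article calls the design a partial randomization preference trial. It still reads the assignment contrast as the impact of preference.

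**Stronger readings that a reader might infer**
- *The PAT-CBT comparison as a whole is confounded.* Within the randomization arm it is not.
- *A separate PAT-CBT test in the preference arm is at risk.* Such a test would take the full bias (2.6%, 3.3% and 5.9% with 60 per cell), but the article lists none. Self-chosen treatment enters through the pooled main effect.
- *The interaction test is flawed.* It asks whether naturalistic selection changes the treatment difference, so patient mix may be part of the question.

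**Conclusion.** The point holds as a minor improvement. The model adjusts for intake symptoms alone, while its assignment factor is self-selected and its treatment main effect mixes randomized with self-chosen patients. Antidepressant use at intake varies by design and could confound both effects.

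The documents do not show that it does. The prognostic gap and the imbalance are both assumed. At the low values every false-positive rate is close to the nominal 2.5%. The 13.5% needs both upper assumptions together with the larger sample size. A reader should not take these rates as estimates of what will happen in this trial; they show only that the bias could range from negligible to a noticeable share of the cited preference effect.

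**What to change.** Add antidepressant use at t0 (yes/no) beside intake symptoms in the Statistical analysis models for two effects: preference versus randomization, and any treatment effect that includes preference-arm patients. Report both as non-randomized, and say that residual confounding remains possible, because one covariate reduces confounding without removing it. The PAT-CBT analysis within the randomization arm and the interaction test need no change on this account.

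The cost is one degree of freedom and a line of wording. Under the assumed imbalance and medicated share, the standard error widens by about 0.5% to 5%. No new data collection should be needed if the medication status checked at eligibility is kept as a t0 variable.

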### Outcome

The primary outcome measures are the Quick Inventory of Depressive Symptoms (QIDS [26]) (independent clinician rating) and the Beck Depression Inventory (BDI-2) one year after initiation of treatment (t4). Treatment response is defined as a decline of at least 50% from t0 (baseline, pre-treatment) to t4 (12 months after intake. Remission is defined by a QIDS-score below 6. A relapse is defined when the criteria of a major depressive disorder (MDD) are fulfilled, for example, a QIDS-score above 9 is documented or hospitalization or outpatient treatment are needed.

Secondary outcome measures include the Beck Depression Inventory (BDI 2 [27]), the QIDS-self-rating, the Symptom-Checklist (SCL-90R [28]), the Depressive Experience Questionnaire (DEQ [29]) and the Dysfunctional Attitude Scale (DAS [30]). Furthermore, we assess social functioning (SOFAS [31]), the Helping Alliance Questionnaire (HAQ [32], and recurrence of depressive episodes assessed by the longitudinal follow-up evaluation interview (LIFE [33]).

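### No intake covariate is stated for the dichotomous outcomes; this matters mainly for QIDS remission and for comparisons that use preference patients

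*Protocol article*

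**What the plan says.** In the Statistical analysis section, the repeated-measures design is followed by the sentence "The variability of intake symptoms is controlled as a covariate". For the time factor, "ANCOVAs with repeated measures and linear regression with autocorrelated data (compound symmetric covariance structure models) are applied". Binary outcomes then get their own sentence: "Dichotomous response scores are examined by tests for frequency distributions and procedures of survival analysis (Coxregression, log-ranktests". No covariate is named for any method in that sentence. The section closes by planning to test whether the PAT-CBT difference depends on assignment.

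The Outcome section gives two binary definitions of different kinds. One is relative to baseline: "Treatment response is defined as a decline of at least 50% from t0". The other is absolute: "Remission is defined by a QIDS-score below 6". The entry criterion in the Participants section is an open-ended floor: "aclinician-rated Quick Inventory of Depressive Symptoms (QIDS-C) score of more than 10 points".

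The Design section expects about half of the patients to choose their treatment: "About 180 patients will have a clear preference foreither PAT or CBT". Table 2 shows that the clinician-rated QIDS and the BDI-2 are both collected at t0.

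**The concern.** The plan treats intake severity as important enough to control for the continuous scores. For binary versions of the same scales it names methods of which two, in their usual form, ignore intake severity, and it does not say whether the third will use it.

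Remission is where this shows. A patient entering at QIDS-C 11 must fall 6 points to reach 5; one entering at 20 must fall 15. The chance of remission therefore depends on where the patient started.

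Two consequences follow. In the randomised arm, precision that is already paid for goes unused. In comparisons that involve preference patients, nothing balances intake severity, so a difference in starting level between the self-selected groups would appear as a difference in remission rate. The adjusted continuous analysis and the unadjusted binary one could then disagree for that reason alone.

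**Working it through.** **The plan's own figure.** The protocol gives no power figure for a binary outcome. Its only calculation (Sample size calculation section) is for a standardised mean difference of 0.50, two-tailed 0.025, power 0.80, with 60 per cell. The standard formula gives 2 × (2.241 + 0.842)² / 0.50² = 76.04, so 77 per cell; power at 60 is 0.69. The 60 is not reproduced. That is a separate matter, and nothing below rests on it: 60 is used only as the planned cell size, and 90 because the Design section's total of about 360 gives 90 in each of four equal cells.

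**Inputs from the protocol.** Difference 0.50 SD; two-sided 0.025; 60 or 90 per cell.

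**Inputs assumed, because the protocol gives none.** Remission 30% in the worse arm; correlation ρ between intake and follow-up score of 0.3 to 0.7; intake difference between self-selected groups of 0.2 or 0.5 SD.

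**Model.** Intake x is standard normal (plus the intake shift in one group). Follow-up y = ρx + √(1 − ρ²)·e − 0.5 × treatment. Remission is y below Φ⁻¹(0.30) = −0.524. Treatment is tested by a likelihood-ratio test from logistic regression without and with x, 3,000 runs per setting. The simulation standard error is about 0.009 for a power near 0.5 (√(0.25/3000)) and 0.003 for an error near 0.025 (√(0.025 × 0.975/3000)).

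**Hand check of the unadjusted power.** Remission in the better arm is Φ(−0.524 + 0.5) = 0.490, so the contrast is 0.300 against 0.490, difference 0.190, mean 0.395. At 60 per cell the null standard error is √(2 × 0.395 × 0.605/60) = 0.0893 and the alternative one is √((0.300 × 0.700 + 0.490 × 0.510)/60) = 0.0876. Power is Φ((0.190 − 2.241 × 0.0893)/0.0876) ≈ 0.46, in line with the simulated 0.46 to 0.48. Unadjusted power does not depend on ρ, so the spread in that column is simulation noise.

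**Randomised arm, power at two-sided 0.025**

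| Per cell | ρ | Unadjusted | Adjusted | Gain (points) |
|---|---|---|---|---|
| 60 | 0.3 | 0.468 | 0.494 | 2.6 |
| 60 | 0.5 | 0.479 | 0.555 | 7.6 |
| 60 | 0.7 | 0.464 | 0.643 | 17.9 |
| 90 | 0.3 | 0.646 | 0.664 | 1.8 |
| 90 | 0.5 | 0.655 | 0.742 | 8.7 |
| 90 | 0.7 | 0.665 | 0.823 | 15.8 |

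A separate simulation, with a chi-square test and remission of 30 to 40% in the worse arm, gave 0.47 against 0.56 at 60 per cell and ρ = 0.5, and a gain of about 2 to 5 points at ρ = 0.3.

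**Preference groups, no treatment effect.** The false difference is 0.30 − Φ(−0.524 − ρ × shift). For ρ = 0.5 and shift 0.5 this is 0.300 − 0.219 = 0.081.

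| ρ | Intake shift (SD) | False difference (points) | Unadjusted error, 60 per cell | Unadjusted error, 90 per cell |
|---|---|---|---|---|
| 0.3 | 0.2 | 2.1 | 0.026 | 0.032 |
| 0.3 | 0.5 | 5.0 | 0.048 | 0.075 |
| 0.5 | 0.2 | 3.4 | 0.037 | 0.038 |
| 0.5 | 0.5 | 8.1 | 0.108 | 0.167 |

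The adjusted test stayed between 0.023 and 0.030 in all eight settings, against a nominal 0.025. It does so because intake severity is the only confounder in the simulation.

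**The case against.** The strongest reply is that this is a condensed article, and that covariates for secondary binary models belong in a full protocol or analysis plan that is not shown. That would settle the matter if the article were silent. It names its tests, however, and two of them do not carry a continuous covariate in standard form. Stratified versions exist, but none is stated.

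A second reply is that the covariate sentence is general and may extend to the Cox model. It may, and the text does not rule it out. Even so, it would leave the frequency and log-rank tests unadjusted.

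A third reply is that the sentence speaks of response scores, and response is already relative to baseline. This stands in part. For the 50% decline the gain can be near zero. Applying the sentence to remission is an inference, made because the article gives no other method for remission.

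A fourth reply is that the sizes rest on assumed inputs, and that the entry floors (QIDS-C above 10, BDI-2 above 17) narrow the intake range and so tend to lower the correlation. This also stands, and it favours the lower end of the ranges.

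A reader might go further and infer that the plan gives binary outcomes only unadjusted tests. It does not, because Cox regression is named. A reader might also infer that the remission part of hypothesis A is tested with too little power. That hypothesis expects both therapies to be effective and ties remission to the LIFE interview; it states no PAT-CBT contrast on QIDS remission, so the power figures above do not describe a test of it.

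**Conclusion.** The point holds in a limited form. The article fixes no intake-adjusted analysis for its binary outcomes, although it controls intake for the continuous ones and collects the scores needed.

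In the randomised arm this is a loss of efficiency and not of validity: about 2 to 5 points of power at a correlation of 0.3 and 8 to 9 at 0.5. In comparisons with preference patients it is a matter of bias whose size depends on an unknown imbalance. The error is at most about 0.04 at 0.2 SD, and about 0.05 to 0.17 at 0.5 SD, against a nominal 0.025, for 60 to 90 per cell and correlations of 0.3 to 0.5. All of these rest on an assumed 30 to 40% remission in the worse arm, an assumed correlation and an assumed imbalance, and they apply to QIDS remission only if it is analysed by the named methods.

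The documents do not support a claim that the primary result is affected: "The primary outcome measures are the Quick Inventory of Depressive Symptoms (QIDS [26]) (independent clinician rating) and the Beck Depression Inventory (BDI-2" at one year are the primary measures, and the covariate sentence sits with the repeated-measures models for such scores. Nor would adjustment make the preference comparison unconfounded. Self-selected patients can differ in other ways, and the t0 score removes only the part due to intake severity. The change is worth making because it is cheap, but it concerns supporting analyses.

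**What to change.** In the Statistical analysis section:

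- Make the main analysis of remission and response at the main assessments a logistic regression with treatment, assignment, their interaction and the t0 score of the same scale (QIDS-C for QIDS-based outcomes, BDI-2 for a BDI-based response). The interaction term also provides, for binary outcomes, the test of dependence on assignment that the section already promises.
- Report a marginal (standardised) risk difference with its confidence interval.
- Put the same t0 score into the Cox models.
- Keep the frequency and log-rank tests as unadjusted support.
- State that the definition and analysis apply to remission as well as to response, and that adjustment addresses only the part of preference-arm confounding that is due to intake severity.

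The cost is a few sentences. The t0 scores are already scheduled for collection, so no new data or patients are needed. The one small downside is that the odds ratio is conditional on baseline, which is why the marginal risk difference should stand beside it.
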